**Introduction**

Multiple Sclerosis (MS) is the most common chronic neurological condition affecting young adults [1]. Women are two times more likely to develop MS than men, and currently, MS affects over 150,000 people in the UK [2]. People are usually diagnosed between 20 and 40 years of age, the prime working years of an adult [3].

MS is characterised by progressive damage to the Central Nervous System (CNS), producing plaques in the brain and spinal cord [4]. These lesions are caused by the loss of myelin sheaths which leads to inflammation and axonal damage (or loss) [1].

Due to the damage to the brain, people with MS can present with a range of physical and cognitive problems. The most common physical problems presented in MS are gait difficulties that can lead to people needing a wheelchair and balance disorders, which lead to an increased risk of falls [5]. In fact, after 15 years with the condition, approximately 50% of people with MS need support walking [6].

Furthermore, up to 65% of people with MS present some level of cognitive impairment [7]. Although significant variability exists in the types and intensity of impairments MS can cause, memory and attentional problems are the most frequently reported in this population [7–9].

To this array of physical and cognitive impairments, MS is also characterised by the presence of “invisible symptoms”, which are symptoms not visible to others. Some invisible symptoms are fatigue, pain, bladder and bowel problems, and vision difficulties, among others [10]. From these, fatigue is the most reported symptom in MS (approximately 90% of people with MS) [11].

The range of physical, cognitive, and psychological problems that people with MS can present increases the personal and professional challenges that people with MS experience at work [12].

Vocational rehabilitation (VR) aims to help people with illness or disabilities to remain, return to or find new employment. We have previously developed a VR intervention to support people with MS to remain in paid employment called MSVR (multiple sclerosis vocational rehabilitation) [13]. We have tested this programme in a community setting [14], and within the NHS [15]. However, we found barriers (e.g., lack of staff, service structure, etc.) to deliver this programme within a healthcare setting [15,16]. Patient and public involvement (PPI) representatives suggested testing this programme within the services provided by MS charities.

Before conducting a larger study, the feasibility of delivering VR through MS charities needs to be established. This study was informed by the Medical Research Council (MRC), which provides guidance for developing complex interventions [17].

**Aims**

The primary aim is to assess the feasibility and acceptability of conducting a multicentre, parallel-group RCT comparing MSVR delivered to participants recruited from MS charities with existing services offered by the charities alone. More specifically, we will focus on:

1. Recruitment: To assess the length of time to recruit the sample planned, the recruitment rate, the proportion of eligible patients recruited, reasons for non-recruitment, and the appropriateness of study characteristics such as inclusion and exclusion criteria.
2. Retention and engagement: To estimate the proportion of participants lost to follow-up and the reasons for loss to follow-up, withdrawal rates, data completeness, and participants’ compliance with MSVR and identify factors affecting compliance.
3. Intervention delivery: To assess feasibility of delivering up to 10 hours of VR over 6 months, intervention fidelity, intervention adherence, feasibility of delivering VR alongside existing services of the charities, and practical issues related to intervention delivery.

The secondary aims are to determine parameters for a sample size calculation for a future large-scale RCT and explore the mentoring and training needs of the MSVR champions (i.e., employees from MS charities recruited to deliver the intervention) recruited for the study.

This study includes an embedded mixed methods process evaluation, the aims of which are to understand acceptability and usefulness of:

- MSVR for people with MS, employers, and MSVR champions.
- study procedures to MS charities and participants.
- MSVR training manual, sessions, and mentoring support.

**Methods and Analysis**

This is a multicentre, feasibility, parallel-group RCT with an embedded mixed methods process evaluation. Participants will be randomised (1:1 ratio) to receive either MSVR plus usual care (UC) or UC alone. This study will be reported following the CONSORT 2010 statement: extension to randomised pilot and feasibility trials [18].

**Eligibility criteria**

The study will recruit people with MS (1) between 18 and 65 years of age, (2) who can give informed consent, (3) who can communicate in English, and (4) who are in paid employment (including self-employed). This study will exclude participants who are planning to retire within the next 12 months or are currently receiving vocational rehabilitation support.

If a participant with MS consents to involving their employer in the intervention, they will be included if they are (1) between 18 and 65 years of age, (2) can give informed consent, (3) can communicate in English, and (4) is currently employing a person with MS. We will consider the line manager or a human resources representative as the employer of the person with MS. There are no exclusion criteria for the employers.

MSVR champions (i.e., employees from MS charities recruited to deliver the intervention) will be asked to complete a consent form to complete a demographic and skills questionnaire and participate in an interview at the end of the study.

**Setting and locations**

The University of Nottingham will coordinate this study, which will involve up to six MS charities. The charities will be purposively recruited based on their attributes (e.g., organisation size, resources, and services available), and interest in optimising their existing services. The intervention will be delivered remotely via Microsoft Teams and/ or telephone, according to the participant’s preferences. The study will be conducted between June 2025 and November 2027.

**Recruitment**

Participants with MS will be recruited through the participating MS charities over a 10-month period. The organisations will share information about the study using a multi-pronged approach to reach a broader range of people with MS. Therefore, the study will be advertised on their helplines, social media, websites, and bulletins.

The initial approach to potential participants with MS will be made by the MS charities employees through their helpline support, newsletters, and events. They will provide information about the study using a study advert and participant information sheet (PIS). People with MS declining the opportunity to participate will be asked for a reason for not participating, but they do not have to reply.

We will develop a recruitment matrix to ensure we recruit a diverse sample of participants to the feasibility trial. The matrix will include information such as ethnicity, socioeconomic status (based on deprivation index), gender, age, and employment characteristics.

People with MS will also have the opportunity to read about the study online (e.g., social media, websites, bulletins). If a person with MS is interested in participating, they will be asked to complete an expression of interest with the charity worker to consent for their details to be shared with the researcher or to contact the lead researcher via telephone or email.

Those people with MS who are interested in participating in the study will be told that they can include their employer (e.g., line manager or human resources representative) in the intervention to receive information and advice about MS at work. It is not mandatory for the person with MS to include their employer, and if the person with MS does not consent to include their employer, the employer will not be contacted.

**Screening and informed consent**

Potential participants with MS will be contacted via telephone to be screened against the inclusion criteria by the lead researcher (BDP). A screening log will be used to monitor and record information about participants screened and reasons for not being recruited.

**Intervention: MSVR**

The full description of the intervention is presented elsewhere [13]. Due to feedback from previous studies [15], the intervention was extended to support the person with MS over six months (instead of the original three months).

MSVR will be delivered by employees from MS charities currently working within MS charities supporting people with MS with advocacy or information provision. These employees have a wide range of professional backgrounds, expertise in MS (including symptoms and progression), skills with active listening, and have been trained to handle difficult conversations. The workers from MS charities, called “MSVR Champions”, will receive training and mentoring in preparation for the trial.

MSVR for people with MS involves an initial interview (including vocational goal setting), followed by up to 10 hours of individually tailored support according to need. The support will focus on supporting the person with MS to meet their vocational goals by addressing topics such as:

- Understanding MS
- Advice on reasonable adjustments (e.g., modification to the work environment or duties to accommodate the impact of MS)
- Support requesting reasonable adjustments
- Fatigue management
- Managing cognition at work
- Information about legal rights
- Disclosure (i.e.., telling the employer or colleagues about the MS diagnosis)
- Long-term career planning (i.e., exploring alternative career options)
- Managing mood difficulties
- Signposting to local and national resources.

The intervention addresses the individual needs of the person with MS and offers advice remotely (e.g., via telephone, videoconference, or email). The sessions will be arranged at a time convenient for the person, and the support needed will vary according to the complexity of their workplace difficulties. Participants will receive a brief written summary of the content discussed in each session via email with further resources to complement the knowledge gained.

MSVR for the employers will involve an initial interview (approximately 30 minutes) to understand their experiences supporting the employee with MS and up to 4 hours of support over the six-month intervention. The employer’s intervention includes:

• Signposting to relevant organisations.

• Educational resources.

• Information about MS and invisible symptoms.

• Support with providing reasonable adjustments.

• Legal responsibilities (Equality Act).

After each session, the employer will receive an email summarising topics discussed and, when required, a list of actions they should complete before the next session.

**Control Condition**

Participants (MS and employers) in the control group will receive resources from the MS charities' websites, helplines, and events. Due to the nature of the study, usual care will vary between participants in the control group. However, no MS charity recruited for this study will have a specialist vocational rehabilitation service (and none should have indicated that they will be creating such a post soon).

Participants (MS and employers) in the control group will interact with members from the MS charity who have not been trained and are not involved in MSVR delivery to reduce the potential for contamination.

At the end of the study, participants with MS in the control group will receive the “Work and MS: An Employee’s Guide” booklet from the MS Society, which contains information about MS and work. PPI representatives suggested this to reduce the burden of being allocated to the control group and encourage the completion of follow-up questionnaires.

*Concomitant Therapy*

Participants will continue to use services from social care, the National Health Service (NHS), and other third-sector organisations alongside MSVR. Information on any concomitant therapy received will be collected using a resource use questionnaire.

**Monitoring and Mentoring**

An Occupational Therapist (OT) (JH) with extensive working experience in VR for people with long-term health conditions will offer monthly mentoring sessions to the MSVR champions.

The mentoring sessions will be conducted in groups via videoconference to discuss cases, confidentiality issues, contamination, and challenges during the intervention delivery. MSVR champions will also be able to request further mentoring if a query appears outside the mentoring sessions.

The OT will complete a mentoring record form to capture topics addressed and questions raised by the MSVR champions during the mentoring sessions to gain further understanding of the skills needed to deliver MSVR and additional training needs.

**Primary and secondary outcomes**

The primary outcomes assess the feasibility and acceptability of delivering MSVR within the context of MS charities by measuring recruitment, retention and engagement, and intervention delivery.

Secondary outcomes refer to determining the parameters for a fully powered trial, including selecting a primary outcome measure, sample size estimation, intervention costs, and identifying intervention improvements and further training needs of MSVR champions. The feasibility outcomes are summarised in Table 1.

**Table 1 Feasibility outcomes and measures**

| Feasibility objectives | Outcomes and measurement |
| --- | --- |
| To assess the feasibility and acceptability of MSVR | **Recruitment**  Length of time to recruit the sample will be calculated using the date of the first and last participant recruited to the feasibility trial  Number of participants with MS screened, meeting the inclusion criteria, recruited and randomised.  Number and reasons of participants not fully meeting the inclusion criteria.  **Retention and engagement**  Number of participants lost to follow-up  Number of participants who withdraw from the intervention  Amount of missing data from questionnaires  Number of participants who complete the initial interview and at least two intervention sessions.  **Intervention delivery**  Hours of support delivered, and number of sessions attended by the participants with MS and employers.  Number of participants who do not attend sessions and number of early dropouts  Hours of support delivered per intervention component and number of participants completing the intervention as structured.  Number of mentoring sessions attended by each MSVR champion.  MSVR champions attendance to training and barriers to delivering the intervention within existing services.  **Acceptability**  Feedback on the intervention content, delivery mode, and structure. |
| To plan for a fully powered trial] | **Selection of primary outcome measure**  Determined by importance of different outcome measures, response rates, and missing data of outcome measures on questionnaires, and preliminary effect size estimates of the outcome measures.  **Sample size**  To estimate the standard deviation of the continuous primary outcome measure with a 95% confidence interval, including lost to follow-up and data completeness.  **Intervention cost**  Cost of MSVR champions and mentor’s time. |

**Outcome measures**

Outcomes measures will be assessed at the end of the intervention and 3-, 6-, and 12-months post-intervention. The measures collected and time points have been summarised in Table 2.

**Table 2 Summary of assessments and time points**

| Activities / Measures | Assessment and time-point | | | | | | |
| --- | --- | --- | --- | --- | --- | --- | --- |
|  | **Screening** | **Baseline**  **(A1)** | **Intervention** | **End of Intervention**  **(A2)** | **3 months FU** | ***6 months***  ***FU*** | ***12 months***  ***FU*** |
| Screening for eligibility | x |  |  |  |  |  |  |
| Completion of consent form | x |  |  |  |  |  |  |
| Demographic information | X |  |  |  |  |  |  |
| Randomisation | x |  |  |  |  |  |  |
| Goal Attainment Scaling |  | x | **MSVR Intervention** | x | x | x | x |
| 36-item short form health survey |  | x |  | x | x | x | x |
| Perceived Difficulties Questionnaire |  | x |  | x | x | x | x |
| Work Productivity and Activity Impairment Questionnaire for MS |  | x |  | x | x | x | x |
| Modified Fatigue Impact Scale -5 Items version |  | x |  | x | x | x | x |
| EQ-5D-5L |  | x |  | x | x | x | x |
| Generalised anxiety disorder scale |  | x |  | x | x | x | x |
| Patient health questionnaire 8-item scale |  | x |  | x | x | x | x |
| General self-efficacy scale |  | x |  | x | x | x | x |
| Workplace Accommodations questions |  | x |  | x | x | x | x |
| Resource use questionnaire |  | x |  | x | x | x | x |
| Adverse events |  |  | x |  |  |  |  |
| Intervention cost (training, mentoring, intervention delivery) |  |  | x |  |  |  |  |
| Acceptability of MSVR (interviews with people with MS and employers) |  |  |  | x |  |  |  |
| Acceptability of training (MSVR champion questionnaire) | x |  |  |  |  |  |  |
| Acceptability of MSVR and mentoring (interviews with MSVR Champions) |  |  |  | x |  |  |  |
| A=Assessment; FU= Follow-up; EQ-5D= European Quality of Life- 5D; MS= multiple sclerosis; MSVR= Multiple Sclerosis Vocational Rehabilitation | | | | | | | |

The outcome measures will be collected using REDCap, or by post or telephone if a participant cannot access an electronic device. The acceptability measures (i.e., interviews) will be collected remotely via telephone or Microsoft Teams. To minimise missing data, we will set up a REDCap email notification to automatically remind participants to complete the questionnaires 2 weeks from the due date.

Participants completing the questionnaire by post or telephone will be contacted by a member of the research team via email or telephone to remind them to complete the questionnaire. If needed, a second copy of the booklet of questionnaires will be sent by post. Participants will receive priming calls from a member of the research team to remind them to complete the questionnaires.

*Participants with MS*

This feasibility study has two candidate coprimary outcome measures for a future definitive trial: (1) health-related quality of life as measured by the 36-item short form health survey (SF-36) [19] and (2) work productivity, measured using the Work Productivity and Activity Impairment (WAIP) for people with MS [20], extending the recall period from seven days to four weeks. These measures have been identified as relevant in other studies about MS and employment [21,22].

The SF-36 measures eight health constructs relating to physical and mental health. This measure has a high internal consistency (Cronbach’s alpha >0.80) and good test-retest reliability (>0.70). The WAIP:MS measures absenteeism and presenteeism, productivity loss and activity impairment. Higher scores in the WAIP:MS represent a higher impact of MS at work and conducting everyday activities.

The European Quality of Life with five dimensions (ED-5D-5L) [23] will assess psychological and health-related quality of life, focusing on mobility, self-care, usual activities, pain/discomfort, and anxiety/ depression. Cognitive difficulties will be measured with the perceived deficits questionnaire (PDQ) [24,25], a 5-point Likert scale 20-item questionnaire with four sub-scales with a 0.93 Cronbach alpha. The sub-scales have good reliability and internal consistency: Cronbach’s alpha .78

(attention/concentration), .84 (planning/organization), .83 (retrospective memory),

and .76 (prospective memory) [26]. Fatigue will be assessed using the modified fatigue impact scale 5 (MIFS-5), a 4-point Likert scale with five items [27]. The General Self-Efficacy Scale (GSES) assesses the participants’ belief in their ability to complete tasks successfully [28]. Two brief questionnaires will assess mood: the Generalised Anxiety Disorder Scale (GAD-7) [29] and the Patient Health Questionnaire (PHQ-8) [30].

Vocational goals will be measured using the goal attainment scale (GAS) [31] to ascertain the impact of the intervention on the vocational goals set by participants at the beginning of the study. Workplace accommodations will be assessed using a series of binary questions (yes/no) about support received at work.

Finally, a resource use questionnaire will be developed to record the healthcare utilisation and additional services and support accessed during the feasibility trial.

*Employers*

Employers will be asked to complete three questions regarding their knowledge of MS, confidence in managing the employee with MS at work, and confidence in their ability to solve future problems at work.

*MSVR Champions*

MSVR champions will be asked to complete the educational course assessment toolkit (EDUCATOOL) [32]. A 12-item questionnaire to evaluate the training and learning experience of the MSVR champions during the study.

**Progression Criteria to the Future Trial**

Progression criteria will be assessed based on recruitment and follow-up rates after 4 months of recruitment based on a traffic light system of green (go), amber (review), and red (stop) [33]. The start of recruitment is defined as the first participant recruited into the trial.

Recruitment criteria will be assessed over months 3-4 to allow recruitment rates to stabilise. The follow-up criteria will be assessed at the end of the intervention. Feasibility will be demonstrated if:

- At least six people with MS are recruited per month across all sites (green), at least three but less than six (amber), or less than three (red).
- Percentage of participants randomised to the MSVR arm who complete the intervention (initial interview and at least one session), at least 80% green, at least 40% but less than 80% (amber) or less than 40% (red).
- The follow-up rate criterion is assessed by the percentage of people who complete the end of intervention survey with at least 80% (green), at least 65% but less than 80% (amber) or less than 65% (red).

If the rescue plan is not effective (e.g., progression criteria measures do not progress to amber or green), and any criteria are graded as red, we will not progress to the definitive trial. The findings from the progression criteria stages throughout the trial will be used to inform the full-scale future trial.

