**Sample size**

A pragmatic target of 60 participants with MS (30 in each arm) was estimated based on personal communications with the MS charities recruited for the study and experiences from previous studies [14,15]. This figure aligns with recommended sample sizes for feasibility trials to estimate a parameter for a future RCT [34–36]. This sample size will provide sufficient data to achieve the study aims mentioned above.

Participants with MS will be asked if they are interested in recruiting their employer to the intervention, where they will receive information and advice about MS and employment. Based on previous research studies [14,15], we anticipate that approximately 20% of participants will consent to include their employer.

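### The follow-up progression criterion names no arm, so an overall green can, in a narrow set of results, coexist with control-arm follow-up below the protocol's own red line

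*Protocol*

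**What the plan says.** Under Progression Criteria to the Future Trial, the protocol lists three traffic-light criteria. The follow-up criterion is "The follow-up rate criterion is assessed by the percentage of people who complete the end of intervention survey with at least 80% (green"), then "at least 65% but less than 80% (amber) or less than 65% (red"). Its timing is fixed: "The follow-up criteria will be assessed at the end of the intervention".

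The criterion listed just before it does name an arm: "Percentage of participants randomised to the MSVR arm who complete the intervention (initial interview and at least one session"). The recruitment criterion is a count over all sites. The stop rule acts on the listed criteria only: if the rescue plan does not work and "any criteria are graded as red, we will not progress to the definitive trial".

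The Sample size section gives "A pragmatic target of 60 participants with MS (30 in each arm"), and Methods and Analysis gives the allocation: "Participants will be randomised (1:1 ratio) to receive either MSVR plus usual care (UC) or UC alone".

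Under Control Condition, control participants are promised a booklet at the end of the study, on the advice of patient representatives, "to reduce the burden of being allocated to the control group and encourage the completion of follow-up questionnaires". Under Data analysis, loss to follow-up goes into the CONSORT diagram and outcome measures are summarised by group. Neither is linked to the traffic-light grade.

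**The concern.** The study asks whether a parallel-group randomised trial is feasible, and retention is a named part of that question. Unequal loss between arms is the kind of attrition most likely to bias the comparison in a definitive trial. A single percentage over both arms averages such a difference away, because very high completion in one arm can offset poor completion in the other.

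Unequal loss is plausible here. Participants know their allocation. The MSVR arm is offered an initial interview and up to 10 hours of individual support, while the control arm has the charities' ordinary resources. The booklet shows that the authors thought about questionnaire completion among controls, yet no progression criterion checks completion in that arm. At stake is whether the formal grade could read green while one arm sits where the protocol's own bands would say red.

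**Working it through.** **Inputs.** From the protocol: 60 participants, 30 per arm (Sample size); green at 80% or more, amber from 65% to under 80%, red under 65% (Progression Criteria). The 60 is a pragmatic target with no power calculation behind it, so the only check on it is 30 + 30 = 60, which agrees. The protocol gives no expected completion rates, so all true rates below are assumptions.

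**Step 1: thresholds as counts.**
- Overall green: 0.80 × 60 = 48 completers or more.
- Overall amber: 0.65 × 60 = 39 or more.
- Red line applied to one arm: 0.65 × 30 = 19.5, so an arm with 19 or fewer completers is below it.

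**Step 2: which results are green overall with controls at 19 or fewer?** Let m be MSVR completers and c control completers. The conditions are m + c ≥ 48, c ≤ 19 and m ≤ 30. Three pairs satisfy them:

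| MSVR | Control | Overall | Gap |
|---|---|---|---|
| 30/30 (100%) | 18/30 (60.0%) | 48/60 (80.0%) | 40 points |
| 29/30 (96.7%) | 19/30 (63.3%) | 48/60 (80.0%) | 33 points |
| 30/30 (100%) | 19/30 (63.3%) | 49/60 (81.7%) | 37 points |

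The lowest control count compatible with overall green is 48 − 30 = 18. For overall amber it is 39 − 30 = 9, that is 30%.

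**Step 3: how likely is it?** With independent binomial counts, m ~ Bin(30, p_M) and c ~ Bin(30, p_C), the joint probability is the sum of P(m)·P(c) over the three pairs:

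| Assumed true rates, MSVR/control | P(green overall) | P(green overall and control below 65%) |
|---|---|---|
| 80% / 80% | 0.576 | 0.0002 |
| 85% / 75% | 0.577 | 0.003 |
| 90% / 80% | 0.896 | 0.003 |
| 90% / 70% | 0.577 | 0.023 |
| 95% / 65% | 0.578 | 0.108 |
| 97% / 63% | 0.578 | 0.172 |

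**Step 4: effect of a floor of 65% in each arm for green.** The new P(green) is the old one minus the probability that either arm is below the floor while the overall grade is green.
- 80/80: 0.576 before and after.
- 85/85: 0.894 before and after.
- 90/70: 0.577 − 0.023 = 0.554.
- 95/65: 0.578 − 0.108 = 0.470.

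**Step 5: a stricter rule for comparison.** If green required 80% in each arm (24/30 or more in both), P(green) would fall from 0.58 to 0.37 at 80/80 and from 0.90 to 0.59 at 90/80. If the lower-graded arm set the result, P(red) at 80/80 would rise from 0.002 to 0.051.

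**The case against.** An overall completion percentage is a common feasibility criterion, and nothing in the protocol says follow-up should be judged by arm. That the criterion pools the arms is inferred from the absence of a named arm and the contrast with the preceding criterion; the text does not use the word. A statistical analysis plan that is not available here might define the denominator. The inference is still the natural reading, and the protocol itself states the rule.

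The failing region is small. It needs nearly complete follow-up in the MSVR arm, and with moderate differences between arms its probability is a few per cent or less. This stands, and it limits the point to minor.

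A gap of 33 to 40 points would also be visible in the CONSORT diagram, and follow-up is only one of three criteria, so green on it alone does not clear progression. Both are true, but visibility does not change the grade that the rule returns.

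Two stronger readings are tempting and are not supported. A reader might infer from the booklet that the protocol expects lower completion among controls. The text describes a measure to encourage completion and predicts no rate, and the reminders and priming calls under Outcome measures are not restricted to one arm. A reader might also infer that the overall percentage would mislead the sizing of the future trial. No section says that the progression percentage feeds that calculation; Table 1 lists loss to follow-up and data completeness separately under sample size.

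**Conclusion.** The point holds as a minor weakness in the decision rule. As written, the follow-up criterion cannot register differential loss. Overall green is compatible with control follow-up of 60% or 63%, and overall amber, which calls for review and does not stop progression, with control follow-up as low as 30%. Green with controls below the red line is rare unless true completion is about 95% or more in the MSVR arm and about 65% or less in the control arm. The sizes rest on three assumptions: the criterion covers both arms together, exactly 30 are randomised to each arm, and completion is independent between participants at the assumed rates. It does not follow that the rule would often clear a trial with failing control follow-up, or that such a difference is expected here.

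**What to change.** Keep the overall 80% and 65% bands. Add one sentence to Progression Criteria to the Future Trial: green on follow-up also requires completion of at least 65% in each arm; otherwise the criterion is graded amber and reviewed. Report the between-arm difference in completion of the end-of-intervention survey with its 95% confidence interval. That also informs the review when the overall grade is amber, a case the floor does not touch.

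No new data are needed. The cost is a lower chance of green when loss truly differs: 0.577 to 0.554 at 90/70 and 0.578 to 0.470 at 95/65, the latter being where the floor is meant to act. With equal arms the chance is essentially unchanged (0.576 at 80/80, 0.894 at 85/85).

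Grading each arm separately and letting the lower grade decide is not recommended. With 30 per arm it would often downgrade a trial with no differential loss, cutting the chance of green from 0.58 to 0.37 at 80/80.
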